## Methods

2

### Patients

2.1

Patient inclusion/exclusion criteria are provided in Table 1. Adult patients with AIS aged 21 years and more (being the age of majority in Singapore) presenting to a single tertiary care hospital treated with IV-tPA as a standard-of-care are eligible for inclusion in this study if systolic BP is elevated (160–180 mm Hg) within 8 hours of symptom onset. Informed consent must be obtained from the patient or their legally authorized representative. Exclusion criteria include a documented allergy to a radiocontrast agent, significant renal impairment (defined with serum creatinine >176 μmol/L or estimated glomerular filtration rate <30 mL/minute), congestive cardiac failure, or allergy to labetalol, the principle IV antihypertensive agent used in the study.

**Table 1 T1:**
[figure not shown]
Inclusion/exclusion criteria for the trial.

### Outcome measures

2.2

We reiterate that all patients included in this clinical trial would have received IV-tPA as standard of care before assessing their eligibility. All patients undergo a baseline clinical evaluation that includes an assessment of severity of neurological impairment according to the National Institutes of Health Stroke Scale (NIHSS), and estimate of their premorbid functional status [according to the modified Rankin scale (mRS); scores 0–2 required for inclusion]. All of them would have undergone a noncontrast brain CT-scan (or magnetic resonance imaging) with or without angiography as per the institutional practice. Information for demographics, risk factors (hypertension, diabetes mellitus, dyslipidemia, ischemic heart disease, smoking, and atrial fibrillation) and use of antihypertensive medications is also collected.

### Randomization and blinding

2.3

All study subjects undergo CT perfusion to obtain the baseline cerebral hemodynamic parameters. Participating patients are randomly assigned to early intensive BP lowering (140–160 mm Hg) or the guideline-based management (160–180 mm Hg) in a 1:1 ratio using a central computer generated sequence with minimization according to age (<60 vs ≥60 years), severity (NIHSS score <10 vs >10), and baseline systolic B (<150 vs >150 mm Hg). The treating physician is unblinded to the treatment assignment as he/she is required to titrate BP control with IV labetalol. However, all 90-day outcome assessments are conducted by physicians who are kept blind to the treatment allocation.

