**Methods::**

In a randomized controlled trial, 54 thrombolysed AIS patients with a systolic BP of 160 to 180 mm Hg will be randomized to early intensive BP lowering (systolic target range 140–160 mm Hg) or guideline-based BP management (systolic range 160–180 mm Hg) during first 72-hours using primarily intravenous labetalol. We hypothesize that early intensive BP lowering will not reduce CBF by 20% and/or increase the volume of hypoperfused tissue by >20% on computed tomographic perfusion. Clinical outcome will be assessed using a dichotomized modified Rankin scale (scores 0–1 as excellent outcome vs scores 2–6 as dead or dependent) at 90 days. Other outcome would be symptomatic intracerebral hemorrhage. The trial is registered at ClinicalTrials.gov, NCT03443596.

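### The minimization cut for baseline systolic BP (150 mm Hg) lies below the whole eligible range, so it does nothing to balance baseline BP; separately, an NIHSS score of exactly 10 has no level

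*Protocol article*

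**What the plan says.** Section 2.3 (Randomization and blinding) allocates patients "in a 1:1 ratio using a central computer generated sequence with minimization" on three factors:

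- age, in two complete levels: "minimization according to age (<60 vs ≥60 years";
- stroke severity and baseline systolic BP, given together: "severity (NIHSS score <10 vs >10), and baseline systolic B (<150 vs >150 mm Hg".

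Section 2.1 (Patients) sets the entry criterion: patients "are eligible for inclusion in this study if systolic BP is elevated (160–180 mm Hg) within 8 hours of symptom onset". The Abstract agrees: "54 thrombolysed AIS patients with a systolic BP of 160 to 180 mm Hg will be randomized".

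Section 2.12 (Statistical analysis) names baseline BP as a covariate, but only where BP itself is being compared. It does not name it for CBF or for hypoperfused volume, which form the primary outcome in section 2.7.

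**The concern.** A minimization factor works only if patients can differ on it. The printed BP cut is 10 mm Hg below the lowest eligible value, so the factor has one occupied level and one that no eligible patient can enter.

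Baseline systolic BP is closely tied to the intervention, because it sets how far pressure must fall to reach the intensive range. The sponsor chose it as one of only three balancing variables in a small trial (54 patients in the Abstract, 30 per group in section 2.11). If the rule is run as printed, that safeguard is absent, and the article does not name baseline BP as a covariate for the perfusion outcome either.

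The NIHSS point is a separate defect in the same sentence. The score takes whole numbers, and the printed levels leave out the value 10.

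**Working it through.** **Step 1. Set the BP cut against the eligible range.** There are 21 whole-number values from 160 to 180 mm Hg. Below 150: 0. Above 150: 21. A reading of exactly 150 also has no level, but no eligible patient can have it.

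**Step 2. What a one-level factor does in the algorithm.** Let the imbalance score for a new patient be the sum, over factors, of (patients in arm A at that patient's level − patients in arm B at that level). For BP the level is always the upper one, so its term is N_A − N_B, the difference in overall arm totals. That term is the same whatever the new patient's BP. It still nudges the arms towards equal size but carries no information on BP.

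**Step 3. Size of the loss, by formula.** Assume BP uniform over 160 to 180 mm Hg and no steering on BP. The SD of one reading is 20/√12 = 5.77 mm Hg. The SD of the difference in arm means is 5.77 × √(2/n):

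- 27 per arm: 5.77 × √(2/27) = 5.77 × 0.272 = 1.57 mm Hg;
- 30 per arm: 5.77 × √(2/30) = 5.77 × 0.258 = 1.49 mm Hg.

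**Step 4. Size of the loss, by simulation of the minimization.** There were 2,000 runs per setting. The assumptions were a biased coin of 0.8, BP uniform over 160 to 180 mm Hg, 35% of patients in one age level and 50% in one severity level. None of these is given in the article.

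| BP factor | SD of arm difference in mean BP, N = 54 | Mean arm difference in count with BP ≥170, N = 54 | SD of arm difference, N = 60 |
|---|---|---|---|
| none | 1.59 mm Hg | 3.0 | 1.49 mm Hg |
| cut at 150 (as printed) | 1.52 mm Hg | 2.8 | 1.53 mm Hg |
| cut at 170 (illustrative) | 0.94 mm Hg | 1.1 | 0.89 mm Hg |

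The printed cut and no BP factor agree within simulation noise, and both agree with step 3. A cut inside the range would lower the SD by about 0.6 mm Hg (1.52 − 0.94 = 0.58 at N = 54; 1.53 − 0.89 = 0.64 at N = 60).

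**Step 5. The same loss as a proportion.** Suppose half of patients lie above 170 (an assumption) and BP is left to simple randomization. The exact binomial chance that the arms differ by 20 percentage points or more in that proportion is 0.134 with 27 per arm and 0.155 with 30 per arm. Under the uniform assumption the two halves have means of 165 and 175 mm Hg, so a 20-point difference moves the arm means apart by 0.20 × (175 − 165) = 2 mm Hg.

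**Step 6. NIHSS.** Scores of 9 or less are in the lower level and scores of 11 or more in the upper. A score of 10 is in neither. The age factor beside it uses ≥ and is complete. The article gives no rule for a score of 10.

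**The case against.** The strongest reply is that the sentence may be misprinted while the program is right. It has a visible slip in the words for systolic BP, and a central program must place a score of 10 somewhere, probably by a fixed rule. That is possible, but the article does not show it, and the ≥ sign prints correctly for age in the same sentence. The text and the program need to be compared.

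A second reply is that the baseline reading used for minimization could differ from the qualifying reading and have fallen below 150. No such second reading is defined, and the Abstract describes the patients to be randomized by the 160 to 180 range.

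A third is that the choice of covariates for the primary model is commonly left to an analysis plan, which is not shown. This stands as far as it goes: the absence of baseline BP from that model in the article is not itself an error. It means only that the article does not show adjustment making up for the inactive factor.

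A reader might also draw stronger conclusions that the documents do not support:

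- *Baseline BP is not balanced at all.* Allocation is still random and 1:1, so BP is balanced in expectation. What is missing is the extra balance that minimization was meant to add.
- *The BP factor adds nothing to the imbalance score.* It adds the overall arm totals (step 2).
- *The NIHSS gap makes BP balance worse.* It has no bearing on BP.
- *The 13% to 16% chance shows a serious imbalance.* The event is worth about 2 mm Hg in arm means, within an eligible range only 20 mm Hg wide.
- *The treatment comparison is biased.* A chance imbalance in one covariate does not bias a randomized comparison or inflate its type I error.

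**Conclusion.** The point holds as an error in a stated allocation rule, of moderate severity. Taken as written, one of the three minimization factors cannot act on the variable it names, and one NIHSS score has no level. The first conclusion follows from the printed thresholds and eligibility range alone, provided that the baseline reading is the qualifying one. The second needs no assumption.

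The size does rest on assumptions. With BP uniform over the eligible range, the SD of the arm difference in mean baseline systolic BP is about 1.5 mm Hg instead of about 0.9 mm Hg with a cut at 170. A BP distribution bunched at one end of the range, or a different coin probability, would change these figures. The factor would stay inactive in either case. The validity of the randomized comparison is not threatened, and no loss of power or change in the primary conclusion has been shown.

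**What to change.** - Reconcile the BP minimization cut with the eligibility range by using a cut inside that range. A split of <170 vs ≥170 mm Hg is an illustration; the sponsor may prefer the expected median.
- Write the severity factor as <10 vs ≥10.
- Check the live randomization program against the text. If the program already uses workable thresholds, correct the text only. If it uses the printed ones, change it and record the date, so that patients allocated before and after can be told apart. State how any patients with a score of 10 were handled.
- Name continuous baseline systolic BP as a covariate in the primary perfusion analysis. This also covers patients already randomized, for whom the allocation cannot be changed.

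The cost is a short amendment, two thresholds in the randomization program and one covariate that is already collected. No extra patients or data are needed. The change to the program is worth most before further patients are allocated.

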### Intervention

2.4

Patients allocated to early intensive BP lowering are to receive IV labetalol according to a predefined protocol (Table 2), whereas those assigned guideline-based BP management receive current standard of care. All study participants are closely monitored and a CT perfusion scan is repeated at 24 and 72 hours postrandomization. The treatment regime is an initial IV bolus (5–10 mg each, repeated at 10-minute intervals, maximum dose 80 mg) followed by continuous IV infusion to maintain the desired BP.

**Table 2 T2:**
[figure not shown]
Protocol for blood pressure control in thrombolysed acute ischemic stroke patients.

### Background care

2.5

All patients will be managed in a high-dependency stroke unit with repeated neurological examination using the NIHSS, noninvasive BP, and heart rate monitoring (consistent recordings using automatic devices, every 15 minutes for 1 hour, then hourly for 23 hours, then 6 hourly until discharge). All BP measurements are obtained from the nonparetic arm. Rescue endovascular intervention (before inclusion into the study and randomization) is allowed according to local institutional practice. Figure 1 describes the workflow in the study.

**Figure 1 F1:**
[figure not shown]
Study workflow. BP = blood pressure, CT = computed tomographic, IV-tPA = intravenous tissue plasminogen activator, NIHSS = National Institutes of Health Stroke Scale.

### Data collection and follow-up

2.6

All patients undergo repeat CT-perfusion scans at 24 and 72 hours postrandomization, to obtain the estimates of the effects of BP on various cerebral perfusion parameters. NIHSS scores are assessed daily until day 7 (or hospital discharge, if earlier) (Table 2). Patients are followed-up at day 90, where the NIHSS and mRS scores are reassessed. These assessments are conducted in-person by trained staff who are blind to the treatment allocation.

### Outcomes

2.7

The primary outcome is the assessment of CT perfusion studies and evaluate whether CBF in the affected region reduces by >20% and/or the volume of hypoperfused tissue increases by >20% if BP is treated intensively during the first 72 hours in thrombolysed AIS patents. Secondary endpoint is dependency at day-90, defined by scores 2 to 6 on the mRS. Secondary outcome would be sICH, defined by the Safe Implementation of Thrombolysis in Stroke-Monitoring Study (SITS-MOST) criteria as large local or remote parenchymal ICH (type 2) combined with a neurological deterioration (≥4 points on the NIHSS) from baseline or death within 36 hours.^[20]^ Data are entered prospectively on to case report forms without any personal identifiers.

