## Introduction and rationale

1

Elevated systolic blood pressure (BP), defined as >140 mm Hg, is commonly observed in patients with acute ischemic stroke (AIS).^[1]^ Potential mechanisms and associations include pre-existing hypertension,^[1]^ activation of neuroendocrine systems,^[2]^ stress of hospitalization,^[3]^ location of the infarct,^[4]^ stroke subtype,^[5]^ severity,^[6]^ and a homeostatic response to raised intracranial pressure.^[7]^ Whether treatment of this acute hypertensive response improves clinical outcome is unknown.^[7,8]^ Arguments in favor of treatment include the strong positive relationship between degree of elevation in BP and death or dependency,^[9]^ cerebral edema,^[10]^ early and late stroke recurrence,^[11,12]^ and extrapolation of potential benefits in acute intracerebral hemorrhage (ICH).^[13–15]^ Arguments against treatment center on the natural tendency for BP to normalize within a few days of presentation,^[1,5,6]^ and potential harms associated with altered cerebral perfusion related to dysfunction of autoregulation.^[7,16,17]^ Some studies suggest that adverse outcomes are associate with early antihypertensive therapy.^[18,19]^

The primary aim of the study is to determine the effect of early intensive BP lowering (systolic BP target 140–160 mm Hg) initiated within 6 hours of symptom onset and maintained for 72 hours in AIS patients treated with intravenous tissue plasminogen activator (IV-tPA) on cerebral blood flow (CBF), measured with computed tomographic (CT) perfusion imaging. We hypothesize that this treatment approach is safe and that such magnitude of BP lowering does not reduce CBF by 20% and/or increase the volume of hypoperfused tissue by >20% on CT perfusion or adversely affect functional outcomes at 90 days. Secondary aims are to obtain preliminary estimates of the clinical impact of early intensive BP lowering on functional outcomes and symptomatic intracerebral hemorrhage (sICH).

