### Statistical analysis

2.12

Data will be analyzed blind to treatment group according to the intention-to-treat principle by an independent biostatistician. Continuous variables will be presented as mean (SD) and nominal variables tabulated as absolute and/or relative frequencies. Comparisons between binary outcomes will be performed using Fisher exact test. Continuous variables will be compared using the unpaired *t* test and Mann-Whitney *U* test as indicated. Comparisons of BP and NIHSS scores between the 2 groups at different time-points will be analyzed using repeated-measures analysis of variance for the overall effect. Finally, the relative changes in BP, CBF, and NIHSS scores at 1, 24, and 72 hours after the initiation of treatment, and 90-day outcomes, will be compared using analysis of covariance. Baseline BP and use of antihypertensive medications before admission will be used as covariates in analyses of BP differences. Baseline NIHSS will be used as a covariate in analyses of stroke severity. Statistical significance is set at the 5% level. There would be no interim analysis (Table 3).

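### Premorbid mRS 2 is eligible yet day-90 mRS 2–6 counts as dependent, and the wording places this binary endpoint under both Fisher's test and ANCOVA

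*Protocol article*

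**What the plan says.** All places are in the protocol article.

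- **Entry.** Outcome measures (2.2) sets the premorbid mRS criterion: "scores 0–2 required for inclusion".
- **Endpoint.** Outcomes (2.7): "Secondary endpoint is dependency at day-90, defined by scores 2 to 6 on the mRS". The abstract makes the same cut: "scores 0–1 as excellent outcome vs scores 2–6 as dead or dependent) at 90 days". Neither place adjusts the cut for premorbid status.
- **Test for binary outcomes.** Statistical analysis (2.12): "Comparisons between binary outcomes will be performed using Fisher exact test".
- **Test for day-90 outcomes.** Later in the same section, relative changes in BP, CBF and NIHSS are listed, "and 90-day outcomes, will be compared using analysis of covariance".
- **Covariates.** For BP differences the section names baseline BP and prior antihypertensive use. For severity: "Baseline NIHSS will be used as a covariate in analyses of stroke severity". None is named for the mRS.
- **Day-90 measures.** Data collection and follow-up (2.6): "Patients are followed-up at day 90, where the NIHSS and mRS scores are reassessed".
- **Minimization factors.** Randomization and blinding (2.3) uses age, NIHSS and baseline systolic BP. Premorbid mRS is not among them.
- **Role of the endpoint.** Introduction and rationale: "Secondary aims are to obtain preliminary estimates of the clinical impact of early intensive BP lowering on functional outcomes". The same paragraph also hypothesizes that intensive lowering does not worsen 90-day function.

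**The concern.** The entry range and the failure range share the score 2. For a patient already at 2 before the stroke, the best outcome normally expected is a return to 2, and the plan counts that as failure. Such patients add events to both arms and carry little or no information on treatment. The observed difference shrinks, and any chance surplus of these patients in one arm shows up as excess dependency there.

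The second problem is the choice of test. The only day-90 endpoint that the article defines is the dichotomized mRS. One sentence gives it Fisher's exact test. Another, read literally, gives it ANCOVA, which is a model for a continuous response. If both stand, the analyst can choose between them after seeing the data.

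The stake is the credibility of the preliminary clinical estimate, which is the trial's stated secondary aim.

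**Working it through.** **1. Overlap.** Eligible premorbid scores are {0, 1, 2}. Scores counted as dependent at day 90 are {2, 3, 4, 5, 6}. The intersection is {2}. With no return-to-premorbid rule, complete recovery to premorbid mRS 2 is an event in either arm.

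**2. Dilution.** The article gives no event rate, power or sample size for the mRS endpoint, so there is no figure of its own to reproduce. The illustration uses these inputs:
- n = 27 per arm, from Sample size calculations (2.11), where it was derived for the perfusion outcome. The same section gives 30 per arm after the dropout allowance.
- Dependency of 50% versus 70% among patients with premorbid mRS 0–1: an assumption.
- Share f of premorbid mRS 2 patients, equal in both arms and all counted as dependent: an assumption, varied from 0 to 20%.

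The observed rate in an arm is q = f + (1 − f)p, so the observed difference is (1 − f) × 20 points. For f = 10%: 0.10 + 0.90 × 0.50 = 0.55 and 0.10 + 0.90 × 0.70 = 0.73, a difference of 18 points. Power is from full enumeration of Fisher's exact test, two-sided 5%.

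| f | Observed rates | Difference (points) | Power, 27 per arm | Power, 30 per arm |
|---|---|---|---|---|
| 0 | 50.0% vs 70.0% | 20 | 22.7% | 25.9% |
| 5% | 52.5% vs 71.5% | 19 | 21.2% | 23.7% |
| 10% | 55.0% vs 73.0% | 18 | 19.8% | 21.7% |
| 20% | 60.0% vs 76.0% | 16 | 16.6% | 18.3% |

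At 27 per arm the overlap costs 22.7 − 19.8 = 2.9 points of power at f = 10%, and 22.7 − 16.6 = 6.1 points at f = 20%.

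A wider assumed effect, 65% versus 35%, shows the same pattern at 27 per arm: the difference falls from 30 to 27 and 24 points at f = 10% and 20%, and power from 47% to 39% and 33%.

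**3. Chance imbalance.** One patient is 1/27 = 3.7 points of an arm. If a premorbid mRS 2 patient takes the place of a premorbid 0–1 patient whose dependency risk is 50%, the arm's expected rate rises by (1 − 0.50)/27 = 1.9 points. Premorbid mRS is neither a minimization factor nor a named covariate, so nothing in the stated plan corrects for this.

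**4. Test assignment.** Dependency at day 90 is binary, so the Fisher sentence applies. It is also a 90-day outcome, so the ANCOVA sentence applies as worded. Fisher's test takes no covariates, ANCOVA assumes a continuous response, and no covariate is named for the mRS.

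**The case against.** **Impossibility.** A reader might infer that a premorbid mRS 2 patient can never avoid the dependent category, so that the outcome is fixed before randomization. The documents do not say so. The premorbid score is described as an estimate, and a better rating at day 90 is not excluded. Treating every such patient as an event is the natural expectation, but it remains an assumption.

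**Bias.** A reader might infer systematic bias. Allocation is randomized 1:1 and the same cut applies to both arms. What stands is dilution plus chance imbalance.

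**Low power.** A reader might attribute the endpoint's imprecision to the overlap. Near a 50% rate, the 95% CI half-width at 27 per arm is 1.96 × √(2 × 0.25/27) = 26.7 points, and power for 50% versus 70% is 22.7% before any premorbid mRS 2 patient is admitted. Both figures come from sample size alone. Only the fall from 22.7% is due to the overlap.

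**ANCOVA.** The sentence may be meant for day-90 NIHSS, which is measured, and the specific Fisher rule may be meant to govern binary outcomes. Assigning tests endpoint by endpoint is often left to the SAP. This reading is fair and makes the conflict one of wording. However, the words used carry no such limit.

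**Dichotomy.** Cutting the mRS at 0–1 is a deliberate choice for a secondary endpoint aimed at preliminary estimates. Making the ordinal scale the main analysis would be a trade-off. The article's choice is not an error.

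**Conclusion.** The point holds in limited form. As written, full recovery to an eligible premorbid state is scored as dependent. The observed difference shrinks by the factor (1 − f), and premorbid mRS can enter the endpoint through chance imbalance. On the assumed 50% versus 70% at 27 per arm, the loss is about 3 points of power at f = 10% and 6 at f = 20%. This rests on equal shares in both arms and on every premorbid mRS 2 patient counting as an event. The true f is not given.

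The overlap is clear from the text. The Fisher/ANCOVA conflict is real as worded but may be unintended, so it deserves less confidence.

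The no-harm wording in the Introduction asks more of this endpoint than the same paragraph's aim of preliminary estimates. That is a consequence of sample size and would remain without the overlap. It does not show that the article rests a safety conclusion on the mRS: the abstract's conclusion speaks only of physiological effects on perfusion.

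The changes are worth making because they are nearly free.

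**What to change.** 1. Define a good day-90 outcome as mRS 0–1 or return to premorbid mRS, and dependency as its complement. Report the plain 0–1 cut alongside.
2. Name one method for the binary endpoint: Fisher's exact test, or logistic regression adjusted for baseline NIHSS and premorbid mRS. Report the effect with a 95% CI.
3. Limit the ANCOVA sentence to continuous outcomes, such as day-90 NIHSS.
4. Word the functional-outcome part of the hypothesis as estimation, in line with the stated secondary aim.
5. Optionally, add an ordinal mRS analysis as supportive.

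**Cost.** Wording in the protocol or SAP. Premorbid mRS, baseline NIHSS and day-90 mRS are already collected, so no new data, visits or patients are needed. The one downside is that the modified dichotomy is slightly less comparable with trials using plain mRS 0–1, which reporting both cuts addresses.
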